#### Randomization

A computer program will be used to randomize subjects into the intervention or control arm in a ratio of 1:1 using random permutated blocks to optimize balance in each treatment at any given point in time during the study. Treatment assignment will be concealed in sealed envelopes prepared by a third party not directly involved with the study. Treatment assignment will be revealed after the consent form has been signed by the study participant. Due to the nature of this study, we will not be able to blind subjects to their treatment assignments. However, treatment assignments will be concealed from the investigators and the data analyst.

#### Statistical Analysis

Data analysis will be done with Data Analysis and Statistical Software: STATA, version 13 with an alpha of .05 set a priori for all analyses. All participants will be followed up for eight weeks and we will summarize their baseline demographic and technology use characteristics by study arm. Continuous variables will be compared between control and interventions using the *t* test and categorical variables will be compared using chi-square test. All analyses will be based on intention-to-treat in all randomized participants. Our primary outcome, pain intensity, measured longitudinally over eight weeks, will be assessed by mixed model analysis of variance with treatment assignment as between-group factor and time as within-subject factor. Effect sizes will be calculated as mean group differences with standard deviations. A similar approach will be used to analyze continuous secondary outcomes while categorical outcomes will be analyzed by chi-square test.

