#### Data Collection

Data will be collected at various time points (baseline, weeks 2, 4, 6 and 8) as described in Table 1. Data collection for weeks 2 and 6 will be via the IVR system while baseline, midpoint, and closeout visits will be conducted in-person. However, if for unavoidable reasons, in-person visits are not possible, survey questionnaires will be sent via REDCap. Outcome data will be stored in computer network files that are accessible only to IRB-approved study staff. Outcome data will be linked to each subject by a unique number, which will not have any identifying information. All data collected will be analyzed at the end of the study period.

**Table 1 table1:** Data collection schedule: the table depicts the schedule for data collection.

Intervention/Control group data collection	At entry	2 weeks	4 weeks (+/- 5 days)	6 weeks	8 weeks Closeout (+/- 5days)
Enrollment questionnaire	X				
PHQ-8	X				
BPI	X	X	X	X	X
MMAS	X		X		X
BQ- II	X		X		X
FACT-G	X		X		X
ESAS-r	X		X		X
GAD-7	X		X		X
FACIT-F	X		X		X
Opioid consumption	X		X		X
Hospital utilizations					X

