### Statistical Analysis Plan

#### Sample Size Estimation

A sample size of 88 subjects, 44 in each arm, is sufficient to detect a clinically important difference of 1.5 between the control and intervention arms in pain intensity scores assuming equal standard deviation of 2.5, using a two-tailed *t* test of difference between means, with 80% power and a 2-sided alpha of .05. Considering a dropout rate of 20%, the sample size required is 110 (55 per group). Fifty-five participants will be randomly assigned to the intervention and the remaining 55 participants will be assigned to the standard practice of care at the MGH Palliative Care Center (usual care group). Participants will be followed up for a total of 8 weeks.

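### The primary mixed ANOVA gives baseline pain no role as an adjuster, and the 80% power from a single t test does not carry over to every test in that model

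*Protocol article*

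**What the plan says.** Under Sample Size Estimation, "A sample size of 88 subjects, 44 in each arm", is called "sufficient to detect a clinically important difference of 1.5 between the control and intervention arms in pain intensity scores", "assuming equal standard deviation of 2.5". The method is a two-tailed t "test of difference between means, with 80% power and a 2-sided alpha of .05". No visit, or average over visits, is attached to the 1.5 points. A 20% dropout allowance brings the total to 110.

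Under Statistical Analysis, the primary outcome "will be assessed by mixed model analysis of variance with treatment assignment as between-group factor and time as within-subject factor". Treatment and time are the only factors named. The levels of time are not listed. Baseline is mentioned there only for summarising demographic and technology-use characteristics.

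Under Data Collection, "Data will be collected at various time points (baseline, weeks 2, 4, 6 and 8) as described in Table 1", and Table 1 schedules the BPI at all five. Trial Design counts baseline among the repeated assessments. No section gives baseline BPI any other role in the analysis.

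**The concern.** The power statement concerns one difference between two means. The primary model contains a group main effect, a treatment-by-time interaction and contrasts at single visits, and these target different quantities.

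If baseline is a level of time, the group main effect is an average over five visits, one of which precedes treatment and has a true difference of zero by randomisation. A lasting 1.5-point effect is then estimated as 1.2. If baseline is not a level of time, the model as written makes no use of it, although every patient is due to provide it and it is likely to be correlated with later pain.

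At stake is how far the 80% describes the analysis that will be run, and whether precision that costs nothing is used.

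**Working it through.** **Inputs from the article:** difference 1.5, SD 2.5, two-sided alpha .05, 44 per arm before dropout, BPI at baseline and weeks 2, 4, 6 and 8.

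**Assumptions, not in the article:** SD 2.5 at every visit; compound symmetry with within-patient correlation ρ of 0.3, 0.5 or 0.7; true baseline difference zero. Two effect profiles are used: *immediate* (1.5 from week 2) and *linear* (0, 0.375, 0.75, 1.125, 1.5).

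**Step 1: the article's own figure.** n per arm = 2(1.96 + 0.842)² × 2.5²/1.5² = 43.6, rounded up to 44. SE = 2.5√(2/44) = 0.533 and 1.5/0.533 = 2.81. Power is 79.5% by the noncentral t distribution (80.4% by the normal approximation). Dropout: 88/0.8 = 110. The stated figures reproduce.

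**Step 2: group main effect over five visits, baseline included.** The mean difference is (4 × 1.5)/5 = 1.2 (immediate) or 3.75/5 = 0.75 (linear). SE = 2.5√[(1 + 4ρ)/5 × 2/44] = 0.354/0.413/0.465 for ρ = 0.3/0.5/0.7.

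**Step 3: treatment-by-time test, 4 and 344 df, baseline included.** Noncentrality = (44/2) × Σ(dₜ − d̄)²/[2.5²(1 − ρ)]. The sum of squares is 1.8 (immediate) or 1.406 (linear). This gives 9.05/12.67/21.12 and 7.07/9.90/16.50.

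**Step 4: average of the four post-baseline visits.** The mean difference is 1.5 (immediate) or 3.75/4 = 0.9375 (linear). The per-patient variance is 2.5²(1 + 3ρ)/4 unadjusted and 2.5²[(1 + 3ρ)/4 − ρ²] adjusted for baseline.

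**Step 5: week-8 difference adjusted for baseline.** SE = 2.5√[(1 − ρ²) × 2/44] = 0.508/0.462/0.381, against 0.533 unadjusted.

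Steps 2, 4 and 5 use the noncentral t distribution with 86 df, and step 3 the noncentral F distribution.

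| Test, 44 per arm | Immediate, ρ = 0.3/0.5/0.7 | Linear, ρ = 0.3/0.5/0.7 |
|---|---|---|
| Main effect, 5 visits with baseline | 92/82/72% | 56/44/36% |
| Treatment-by-time, baseline included | 66/82/97% | 54/70/92% |
| Post-baseline average, unadjusted | 98/94/89% | 71/60/51% |
| Post-baseline average, baseline-adjusted | 99/>99/>99% | 80/81/90% |
| Week 8, unadjusted t test | 79.5% | 79.5% |
| Week 8, baseline-adjusted | 83/90/97% | 83/90/97% |

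As ρ rises, power falls for the main effect and rises for the interaction. Baseline adjustment raises power for both the week-8 difference and the post-baseline average, so the gain does not depend on which is chosen.

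**The case against.** A reader might infer that the plan makes baseline an outcome visit. The article does not say so: the levels of time are not given, and Trial Design and Table 1 are assessment schedules, not model specifications. The dilution argument is therefore conditional. The post-baseline rows of the table apply if baseline is left out.

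A reader might also infer that the trial is underpowered. The documents do not support that. The sample size arithmetic is correct, and sizing a longitudinal trial on a simple t test is common. Several readings of the model reach 80%. The lowest figures need three things at once: baseline as a visit, the main effect as the primary test, and an effect that builds linearly. With baseline as a level of time, the interaction is the usual test of differential change. It draws on baseline implicitly, which is why its power rises with ρ.

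This is a condensed article. The primary contrast and covariates may be set out in a full protocol or analysis plan that is not shown, so an unnamed test is not in itself an error, and silence on a covariate is not a decision against one. The Abstract's description of the analysis as a repeated-measures mixed model is compatible with an adjusted model.

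All of this stands. It does not remove two facts: the published factor list has no baseline term, and the published power figure belongs to a different analysis. Linear build-up is also not far-fetched, since the Coaching section hopes that patients will be better equipped by the end of the two-month programme.

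**Conclusion.** The point holds as an improvement to the model, not as a demonstrated shortfall. The model as published gives baseline BPI no role as an adjuster. On the natural but unstated reading that baseline is a level of time, its group effect is diluted by a fifth when the effect is immediate (1.5 becomes 1.2). The 80% is correct for a single unadjusted t test, but tests within this model range from 36% to 97% with baseline as a level of time, over the two profiles and the three correlations.

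The size rests on SD 2.5 at every visit, compound symmetry, the assumed correlations and the assumed time course. Restricting baseline pain to at least 4/10 may lower its correlation with later pain and make the gain from adjustment smaller than shown. The documents do not require week 8 as the sole estimand; the post-baseline average is equally defensible for an outcome described as measured over eight weeks.

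**What to change.** In Statistical Analysis, choose one of two equally acceptable forms:

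- model BPI pain intensity at weeks 2, 4, 6 and 8 as outcomes, with treatment, time, their interaction, baseline BPI and baseline-by-time terms; or
- keep baseline among the repeated measures, with its mean constrained equal across arms.

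The two are close but not identical, particularly with missing data, so the text should say which is used. Name one primary contrast, either the week-8 difference or the post-baseline average, at two-sided .05, and report the other as supportive.

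In Sample Size Estimation, state that the 80% refers to an unadjusted t test of a 1.5-point difference on that contrast. Any power quoted for the adjusted model should come with its assumed correlation.

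The cost is wording only: the BPI is already scheduled at entry for every patient, and no extra patients or data are needed. The change should be made before outcome data are analysed.

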### Ethics and Informed Consent

Procedures of our methods have been reviewed and approved by the Dana-Farber/Harvard Cancer Center (DF/HCC) Institutional Review Board (IRB) and the study is registered at [23]. The app is secure and complies with all HIPAA requirements. Subjects will require a secure pass code to be able to access the app. All mobile phone numbers are stored in a secure shared drive available only to IRB-approved study staff. However, if any data breach or adverse effect occurs, the investigator will ensure that they are well-documented and reported according to the IRB’s requirements, regardless of causality.

Potential candidates with upcoming appointments at the Palliative Care Center will receive a letter informing them about the study. The study consent will also be sent along so that interested candidates can review and ask relevant questions during the enrollment visit. During the study visit, subjects will be given sufficient time to review the consent form and will be encouraged to ask questions. A research assistant will go through the consent form with subjects to ensure they comprehend details of the study. Thereafter, subjects will sign two copies of the consent form–one for them and the other for the study team. Patients who want more time to consider participating in the study will be sent home with an unsigned copy of the consent form and encouraged to think about it at their convenience. Should these patients choose to participate, they will be rescheduled for another enrollment visit. After the informed consent process, the research assistant will then perform all other enrollment procedures.

##  Discussion

### Principal Findings

Our expectation is that enabling patients to assess pain control on-demand and empowering them for self-management will lead to improvements in pain and quality of life outcomes. The ePAL mobile application enables patients to assess pain levels, track progression, manage cancer pain and associated symptoms outside hospital settings. Additionally, the app addresses patients’ beliefs that may hinder optimal pain control and also provides an easy way to connect with care providers for timely medication refills. When patients are educated and better understand their cancer and the pain that may be associated with it, improved skills on CP management can be adopted [12,14]. In addition to the capability to generate weekly symptom reports that could be shared with providers, the app also has a notebook function that allows patients to log their symptoms and other relevant questions to ask their care providers at their clinic visits. We hope these functions will facilitate improved patient-provider communication.

Cancer pain, when not managed timely or adequately, may progress to pain crisis necessitating immediate intervention. Pain crisis refers to an episode of severe, uncontrolled pain that causes patients and their caregivers significant distress [9,14]. Epidemiological data on incidence of pain crises in cancer management is scarce but some centers report that pain crises account for about 20-25% of all palliative care referrals [14]. Our intervention has the capacity to identify early on, cancer pain patients that are at risk of experiencing pain crises and eventual hospitalization.

A special concern is that the frequent prompts to assess pain control may cause a heightened awareness of symptoms and increase anxiety in some participants. While this is plausible, we hope that the application will increase self-efficacy for self-management. Therefore, the GAD-7 will be useful in establishing the effect of our approach on anxiety. A study by Kroenke and colleagues showed that a telecare management of pain and depression in patients with cancer actually had a positive effect on anxiety levels and was also associated with improvements in pain control and other quality of life outcomes in intervention participants [24]. Another similar concern is that the frequent pain assessments may also increase opioid use. Rustoen et al’s 6-week trial of PRO-SELF, a self-care intervention for cancer pain management that involved daily logging of pain intensity and analgesic intake, revealed that opioid intake increased significantly in all patients in the study [25]. They also reported that study participants took about 40% higher doses of opioids than reported in previous studies although they speculated that this could be due to the fact that only patients with bone metastases were included in the study [25]. It remains to be determined how ePAL will impact opioid consumption. However, this present study does not require daily logging of pain intensity but suggests pain assessments three times per week.

### Limitations

Given that the sample population is drawn from patients attending the palliative care clinic of a large academic center, majority of these patients may have advanced cancers and complicated diseases. As a result, there is a possibility that some patients may not be able to complete the study or attend final study visits. To limit loss to follow-up and missing data, we limit the participation to patients with life expectancy >2 months. Also, we will measure endpoints at multiple times and use REDCap for those unable to attend the final study visit. Another potential limitation is concerning the external validity of the study: This is because findings from this study may be generalizable to patients in academic medical centers. However, if the intervention proves to be effective in these settings, we believe that it will also be effective in patients receiving care in nonacademic medical centers because the app is patient-centered and easily adaptable to other settings.

### Conclusions

This is one of the first clinical trials evaluating the impact of a multidimensional evidence-based approach to pain management via a mobile phone application. Our hope is that findings from this study could lead to larger, multicenter trials to demonstrate more robust evidence. We also hope that similar evidence-based approaches can be developed for other acute-on-chronic conditions to empower patients for self-care, reduce cost, and improve overall patient outcomes.

## Abbreviations

CP: cancer pain
HIPAA: Health Insurance Portability and Accountability Act regulations
IRB: Institutional Review Board
IVR: Interactive Voice Response
MGH: Massachusetts General Hospital
NCCN: National Comprehensive Cancer Network
NRS: numerical rating scale
RCT: randomized controlled trial
WHO: World Health Organization
